^2^ Planned secondary outcome, examining change between Admission and Discharge for Clinical assessment battery items, and Baseline and Follow-up for Administrative data items

^*^ Planned predictor in hierarchical linear regression modelling, note that for STORI-30 change between Admission and Discharge stage will be used (reduced, stable, increased)

X Collection occasion

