### Measures

#### Primary outcome measure

The primary outcome measure will be change in psychosocial functioning as measured by total score on the HoNOS [37]. It is hypothesised that there will be no significant difference in the mean change in highest total HoNOS score recorded in the 0–12 months prior to CCU commencement and the highest score recorded 0–12 months post CCU discharge for consumers under the clinical and integrated staffing model. The total HoNOS score has been selected as the primary outcome measure as it:Has high validity, reliability and sensitivity to change, as well as routinely informing service policy and planning decisions in Australia [38];Is considered appropriate for tracking changes in social functioning over time, and more sensitive in doing so than the CANSAS (a needs based measure) [39];Has an embedded role in individual outcome assessment in Australia and New Zealand [38, 40, 41] and there is evidence that it is being regularly utilised in care planning [42, 43]Is supported by an established national assessment protocol and training processes to facilitate inter-rater reliability [38], and with evidence to support higher levels of acceptability [44] and completion than the other core measures of routine outcome suite [38]It is used and available across multiple international settings [45], increasing the replicability of the methodology.

Utilising the criterion of the highest (i.e. greatest dysfunction) score in the 12-month period pre and post CCU entry limits the risk of conflating the benefits of active rehabilitation support with the benefits associated with support and accommodation in the CCU setting.

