A total of 15 potential predictors across three logically determined levels (Level 1 – Consumer/Level 2 – Site/Level 3 – Organisational) will be considered (see Table 4). All predictors identified from the recent literature, with the exception of family involvement, are available. Additional plausible predictors to be considered are ‘rehabilitation engagement’ as assessed through the proxy measure of mode of discharge, functional cognition (via Allen’s Cognitive Levels (ACL) [59]), and substance use (via Alcohol Use Disorders Identification Test (AUDIT) [60]). It is hypothesised that consumers who leave the CCU in a planned manner will be more likely to show improvement than those who do not, and that consumers who experience a positive shift in their stage of recovery will be more likely to show improvement. Additionally, it is expected that lower ratings of alcohol related problems at CCU entry will predict favourable outcomes through rehabilitation engagement. Three additional variables relating to the organisation and site (Staffing model/Site/Length of stay) are planned to be included to exclude moderating effects on the Level 1 predictors. Not all of the available predictors will be used in the final multivariate model, as inclusion of such a large number of variables would risk over-fitting to the relatively small sample size [61]. The stopping rule for inclusion of individual predictors will be defined at the significance level of .05.

**Table 4 Tab4:** Planned variables for inclusion in hierarchical linear regression modelling

Level	Rationale	Construct	Measure/variable name	Type
3 - Organisational	Features with potential impact on consumer experience	Peer support	Staffing model	Dichotomous (Clinical/Integrated)
2 - Site		Site/location	CCU Site	Categorical (Bayside/Coorparoo/Logan)
		Length of Stay	LOS	Continuous
1 - Consumer	Based on previous prediction studies	Demographics	Age	Continuous
			Sex	Dichotomous (Female/Male)
			Education (years)	Continuous
		Primary Diagnosis	Diagnosis	Categorical (Schizophrenia/Schizoaffective Disorder/Other)
		Cognition (functional)	ACL	Scaled
		Medication adherence	LSP-16 (Item 5)	Scaled
		Service utilisation	Psychiatric inpatient bed days	Continuous
		Social function	SFS	Scaled
		Baseline disability	LSP-16 (total)	Scaled
	Novel predictors	Recovery orientation	STORI-30	Ordinal
		Rehabilitation engagement	Mode of discharge	Categorical (Planned/Unplanned - Consumer initiated/Unplanned - CCU initiated)

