### Analysis

The quantitative analysis will be undertaken in SPSS Version 22 and statistical significance will be assessed at a level of 0.05:The cohort of consumers utilising the services across the three sites will be defined using descriptive statistics. Differences between the sites and staffing models will be examined using t-tests and chi-squared analyses. Assuming comparability of the cohorts is established it is planned that the data from the two integrated staffing model sites will be able to be combined.In order to answer the question of equivalence of the integrated and clinical staffing model for CCUs, differences in the total HoNOS score pre admission and post discharge will be assessed using a t-test or Mann–Whitney U test depending on the normality of the distribution.The question of whether CCU rehabilitation care results in change in specific clinically relevant outcome domains, will be answered through analysis of the secondary outcome measures. It is anticipated that data from the secondary outcome measures will be dichotomised and subjected to Mann–Whitney U analysis with appropriate correction for multiple comparisons.Predictors of change in psychosocial functioning following CCU care will be explored using hierarchical linear regression modelling. The dependent variable is the same as the primary outcome variable for the overall study, mean change in total HoNOS score pre admission and post discharge from CCU care. The independent variables will be entered cumulatively with the organisational (Level 3) variable considered first, followed by the site related (Level 2) variables and then the consumer (Level 1) variables. A hierarchical approach is appropriate given the expectation of inter-correlation between the predictors [68].

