The naturalistic approach to sample selection confers both benefits and costs. Whilst the defined exclusion criterion aims to facilitate inclusion of only participants initially deemed to align with the model of service, this inclusive approach risks masking the effectiveness and differences between the two treatment arms through the inclusion of participants who do not complete their planned rehabilitation. Whilst the option of a per-protocol analysis approach [34], including only those participants whose CCU discharge was planned, will be available such an approach would not reflect the reality of rehabilitation practice. It has been argued that limited benefits are to be expected through provision of rehabilitation care without consumer engagement in the process [78]. There is an emerging interest in engagement scales for use in residential rehabilitation settings, including adaptation of an established measure used in assertive community treatment [16]. However, the broad suitability of this measure in application has not yet been established. Engagement with rehabilitation support over the CCU stay is not being specifically measured in this study. It is anticipated that the qualitative interviews with consumers will provide rich detail about relative levels of engagement under the two staffing models. Length of stay (whether a consumer remains for the minimum 6-month length of stay detailed in the model of service) will provide an additional proxy measure of engagement.

The longitudinal approach to sampling adds additional complexity to the evaluation. There is an expectation that service delivery will change over time. Generalizability of findings may also be affected by the expectation of incomplete sampling and site related differences in referral patterns. Given this, careful consideration of the characteristics of participants and non-participants at each is site is warranted.

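### The HoNOS-change predictor model omits baseline HoNOS, so markers of pre-admission severity are liable to enter through regression to the mean; separately, three variables known only by the end of the stay are treated as ordinary predictors.

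*Protocol article*

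**What the plan says.** The Analysis section of the quantitative methodology fixes the outcome of the hierarchical regression: "The dependent variable is the same as the primary outcome variable for the overall study, mean change in total HoNOS score". The section on the primary outcome measure defines that change through the "mean change in highest total HoNOS score recorded in the 0–12 months prior to CCU commencement" and the corresponding highest score in the 12 months after discharge.

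The section on planned predictors announces "A total of 15 potential predictors across three logically determined levels", and Table 4 names them. Baseline HoNOS is not in the table. In Table 2 the asterisk meaning "Planned predictor in hierarchical linear regression modelling" stands on LSP-16 and inpatient bed days (both in the column for the year before admission) and on AUDIT, ACL, SFS and STORI-30 (at admission). It stands on no HoNOS cell. Individual predictors are kept by a .05 significance rule.

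Three of the 15 are not known at entry:

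- **Mode of discharge:** "Additional plausible predictors to be considered are ‘rehabilitation engagement’ as assessed through the proxy measure of mode of discharge".
- **STORI-30:** the Table 2 footnote says "note that for STORI-30 change between Admission and Discharge stage will be used (reduced, stable, increased".
- **Length of stay:** Table 4 places it at Level 2 (Site). The Discussion treats it as a further proxy for engagement: "Length of stay (whether a consumer remains for the minimum 6-month length of stay detailed in the model of service".

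Entry is cumulative: Level 3 first, then Level 2, then Level 1.

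**The concern.** There are two separate faults.

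**Missing baseline.** A change score contains the baseline score with a negative sign. Unless pre and post scores correlate perfectly, consumers with a high pre-admission score tend to show a larger fall whatever the care achieved. A variable that tracks the observed pre-admission score can inherit this and look like a predictor of improvement. Bed days and LSP-16 come from the same 12 months as the peak. Bed days have an additional link: a footnote to Table 2 says HoNOS is rated at admission to and discharge from inpatient care, so consumers with more hospital episodes have more ratings, often at acute times, from which the maximum is taken.

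**Variables formed during the stay.** Length of stay, mode of discharge and STORI-30 change may be consequences of the staffing model or of the improvement itself. They do not act through regression to the mean. Their problem is that they are not prognostic factors available at entry, and conditioning on them can distort the coefficients of variables that are.

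What is at stake is the answer to one of the study's listed questions, namely which factors predict psychosocial outcome. A service could conclude that more disabled or more hospitalised consumers gain most when part or all of that pattern comes from how change was computed.

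**Working it through.** **1. Count of predictors.** Table 4 has staffing model; site, length of stay; age, sex, education, diagnosis, ACL, LSP-16 item 5, bed days, SFS, LSP-16 total; STORI-30, mode of discharge, AUDIT. That is 1 + 2 + 9 + 3 = 15, matching the text. None is HoNOS. LSP-16 total carries the construct name of baseline disability, but it is a different scale and does not stand in for the baseline of the outcome.

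**2. Inputs.** n = 60 + 40 = 100 (Sample section) and alpha 0.05 (Analysis section), taken as two-sided. The documents give neither the pre–post HoNOS correlation ρ nor the correlation r of a marker with baseline HoNOS. Both are assumptions and are varied below. The plan states no figure of its own on this point.

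**3. Induced correlation.** Take equal SDs pre and post, change = post − pre (higher HoNOS is worse), and a marker S with no effect on post given observed pre. Then

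corr(S, change) = r(ρ − 1)/√(2 − 2ρ).

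Power by Fisher's z is Φ(atanh|corr|·√97 − 1.96).

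- ρ = 0.4, r = 0.5: −0.30/√1.2 = −0.274; power 0.79.
- ρ = 0.6, r = 0.3: −0.12/√0.8 = −0.134; power 0.26.
- ρ = 0.3, r = 0.7: −0.49/√1.4 = −0.414; power 0.99.

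The negative sign means that worse baseline goes with more apparent improvement.

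**4. Simulation, single predictor** (n = 100, 4,000 repeats per setting). Share of studies in which a marker with no effect given baseline reaches p < 0.05 when baseline HoNOS is left out:

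| ρ | r = 0.2 | r = 0.3 | r = 0.5 | r = 0.7 |
|---|---|---|---|---|
| 0.3 | 23% | 44% | 85% | 99% |
| 0.5 | 17% | 33% | 71% | 96% |
| 0.7 | 12% | 20% | 48% | 79% |

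With baseline HoNOS in the model, all 12 settings give 4.3% to 5.6%.

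**5. Several markers at once.** The plan enters variables cumulatively, so the single-predictor rate is too high for any one marker. With three markers (ρ = 0.4, r = 0.5 each) and 14 noise terms in one model:

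- correlation among markers 0.5: 18% false entry per marker, 50% for at least one of the three;
- correlation among markers 0.3: 34% per marker, 77% for at least one.

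**6. The opposite data model.** Let S track only a stable severity that underlies both scores equally. Change is then uncorrelated with S. The unadjusted model gives 4.4% to 5.6% false entry, while adjusting for observed baseline gives 19% to 93% (ρ 0.3 to 0.7; correlation of S with the stable trait 0.3 to 0.7). Fixing instead the marker's correlation with observed baseline, the adjusted model gives 97% at r = 0.5, ρ = 0.4 and 35% at r = 0.3, ρ = 0.6.

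**7. Level of length of stay.** It differs between consumers at the same site, so it is a consumer-level value. Table 4 puts it at Level 2, and the Analysis section enters Level 2 before Level 1. Every admission characteristic is therefore first tested conditional on how long the person stayed. The other engagement proxy, mode of discharge, sits at Level 1, so one construct is split over two levels.

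**The case against.** The strongest objection concerns the data model. The rates in step 4 hold only if the marker has no effect given the observed baseline, and the return to 5% after adjustment restates that assumption. LSP-16 disability and SFS could be largely stable measures, and then the planned model is right and the adjusted one misleads (step 6). SFS is also taken at admission, outside the window of the peak. This stands, and it is why the model should be reported both with and without baseline HoNOS. It weighs less for bed days, which share the window and are tied to the rating schedule.

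The peak is taken on both sides, before and after, so the use of a maximum does not by itself favour the baseline. This also stands: the issue is the missing covariate, not an asymmetric outcome.

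A reader might infer that severity markers will appear as predictors purely as an artefact, and that such a finding would contradict the literature the protocol cites. The documents do not support that. They give no correlations. The cited finding that lower baseline disability predicts good outcome is not said to concern HoNOS change, and a better end state for less disabled consumers can coexist with larger change in those who start worse. A reader might also run the two faults together, but the stay variables do not act through regression to the mean, and none is formed after the stay.

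The stay variables are included deliberately. The protocol hypothesises effects of planned exit and of a recovery shift, and adds length of stay with site and staffing to exclude moderating effects. For a fixed set of variables, entry order does not alter the final coefficients. It does alter step-wise attribution and any selection that depends on order, and a .05 inclusion rule is in force. The analysis is described as exploratory, and the staffing comparison is tested separately.

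**Conclusion.** The point holds as a risk. The outcome is a change score, the list of 15 omits its baseline, and at least two listed markers come from the same pre-admission window. At n = 100, a marker with no effect given observed baseline would pass the .05 rule in about 12% to 99% of studies when tested alone (assumed ρ 0.3 to 0.7, r 0.2 to 0.7). With three correlated markers in one model the rate was 18% to 34% per marker and 50% to 77% for at least one, in the two settings tried. A marker that reflects only stable severity stays at 5%. Which case applies to which marker cannot be settled from the documents.

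The second fault needs no assumption about correlations: three variables known only by the end of the stay are entered as ordinary predictors, and length of stay is placed at the wrong level and too early.

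Neither fault touches the primary staffing comparison. Both bear on a listed study question, and the change is worth making before the predictor analysis is run.

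**What to change.** 1. Add the highest HoNOS of the pre-admission year as a forced first-step covariate, or equivalently model the follow-up peak on it.
2. Report the predictor model with and without that covariate as a sensitivity check. Where a marker's result depends on the choice, say so and draw no firm conclusion about it.
3. Move length of stay out of Level 2 in Table 4.
4. Enter length of stay, mode of discharge and STORI-30 change in a final block, reported separately and labelled as process associations. Draw conclusions about predictors known at entry from the model before that block. The hypotheses on planned exit and recovery shift are still examined, in the last block.

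The cost is a revised Table 4 and one paragraph of the Analysis section, about one degree of freedom, and one extra model report. No new data are needed, because baseline HoNOS is already collected for the primary outcome.

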### Qualitative methodology

#### Design

A pragmatic approach to grounded theory facilitates the dual goals of developing a rich understanding of phenomena under examination as well as allowing for adaptation of service delivery in response to consumer and staff views. The methodology of the qualitative component of the study has been developed with consideration of the COREQ checklist [69], and it is intended that this will also inform the reporting of results. Semi-structured qualitative interviews [70] will engage participants, over time, to gather information on expectations (0–6 weeks post commencement), experiences (12–18 months post-commencement) and reflections (12–18 months post discharge) on care at the site of interest. A matrix detailing the cells for sequential qualitative data collection based on time of collection, CCU site and stakeholder group is presented in Table 5. The opportunities for data collection are partly constrained by the timeframes of service commencement; cells coloured black reflect information not available or not relevant to the planned study. At the time of publication all Phase 1 consumer and staff interviews have already been completed.

**Table 5 Tab5:** Planned data collection phases, timeframes, focuses and estimated sample size for each cell of data collection

			Clinical staffing model		Integrated staffing model			
			Site 1 (Coorparoo)		Site 2 (Bayside)		Site 3 (Logan)	
	Interview focus	Timeframe	Staff	Consumers	Staff	Consumers	Staff	Consumers
Phase 1	Expectations of care^a^	Commencement		*n* = 4 (6–10)	*n* = 4 (6–10)	*n* = 4 (6–10)	*n* = 4 (6–10)	*n* = 4 (6–10)
Phase 2	Experience of care	12-18 months post-commencement	*n* = 4 (6–10)	*n* = 4 (6–10)	*n* = 4 (6–10)	*n* = 4 (6–10)	*n* = 4 (6–10)	*n* = 4 (6–10)
Phase 3	Reflections on care and transition	12-18 months post-discharge		*n* = 4 (6–10)		*n* = 4 (6–10)		*n* = 4 (6–10)
Number of estimated total interviews			*n* = (6–10)	*n* = (18–30)	*n* = (12–20)	*n* = (18–30)	*n* = (12–20)	*n* = (18–30)
Estimated total sample pool for each site/group (N)			23	20	25	20	20	16

^a^Data on the expectations of care for staff working at the CCU due to this unit being operational prior to study commencement

Numbers presented in brackets reflect the estimated range of interviews for each cell of data collection

#### Sub-sample

A sub-sample of consumers who consent to have their data included in the quantitative analysis from each site will participate in the sequential semi-structured interviews. Within each cell for qualitative data collection, convenience sampling is employed due to the time constraints associated with the collection of expectation data as well as the limited size of the total sample pool in each case. The aim is to be as inclusive as practicable as well as consistent with a grounded theory approach by sampling to achieve thematic saturation. However, the requirements of exhaustive sampling must be balanced against the relatively small sizes of these groups and the need to avoid the possibility of creating real or perceived pressure on staff and consumers to participate if they do not want to. For the integrated staffing model sites, a balance of peer and clinical worker interviews is planned.

A minimum of four interviews will be completed for each cell of data collection prior to determination of the final sample size. We expect the total size for each cell to be between six and ten, but, consistent with a grounded theory approach, sample size will depend on considerations of when, and whether, thematic saturation is reached, as well as the level of interest from each consumer or staff group at each site and time point.

During Phase One consumers commencing at each of the three CCU sites were approached to be involved in the evaluation project during the initial six weeks of their care. Interview participation was prioritized on the basis of earliest provision of consent, and the availability and willingness to complete the interviews at the proposed time. Effort was made to involve the same consumer participants at each of the two subsequent interviewing phases (Phase 2 and Phase 3), with the option to include new participants in the case of attrition or iterative need. Consumer inclusion in the Phase 2 and 3 interviews will be prioritized on the basis of: [1] participation in Phase 1 interviews; [2] balancing consumers who remain resident at the CCU with those who have left; [3] for consumers no longer resident at the CCU balancing those who had planned and unplanned (consumer and CCU initiated) discharges; and [4] availability at the designated interview time. Consumers will be given the opportunity to participate in feedback and discussion sessions regardless of whether or not they were involved in the interviews.

During Phase One staff commencing at the integrated model sites were approached to be involved in the evaluation project in the initial six weeks of their employment. Phase Two will include both the clinical and integrated staffing model sites. Staff interview participation during Phase 1 was prioritized on the basis of achieving a balance of clinical and peer workers from the integrated staffing model sites. Additional considerations in prioritization of interview allocation were the earliest provision of consent and the participant’s availability and willingness to complete the interviews at the proposed time. For the integrated staffing model participants, effort will be made to involve the same staff in the Phase One and Two interviews, with the option to include new participants in the case of attrition or iterative need. Additional considerations in the prioritization of interview allocation for Phase Two staff interviews will be: [1] balancing clinical and peer staff roles at the integrated staffing model sites and [2] proportionate balancing of staff who have stayed on and those who have left at the integrated staffing model sites.

